## 3.3 Study Population

**Inclusion Criteria:** To be eligible to participate in the study, clinics need to be affiliated with UNC HealthCare and have a patient population that includes patients 65 years of age or older. Targeted patients will be ambulatory (not institutionalized), aged at least 65 years old and taking at least one opioid or benzodiazepine medication listed in the design section for > 6 weeks, indicating they are at high risk for falls.

The UNC HealthCare outpatient clinics serve a diverse patient population, including women and minorities. The patient population served varies across clinics and geographical areas. UNC HealthCare coordinates care and manages care for more than 130,000 older adult patients in North Carolina. These beneficiaries are from all over the state. Females comprise 65.5% of the population. Approximately 52% are White, Non-Hispanic, 5.0% are Hispanic, 3.0% are Native American, 2.0% are Asian, and 38% are African American, Non-Hispanic.

To be eligible to participate in the patient focus group, participants need to be a patient in one of the intervention group clinics, 65 years of age and older, and taking at least one opioid or benzodiazepine chronically.

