### **4.2 Screening/Baseline Visit Procedures and Observation Procedures for the Cluster-Randomized Trial:**

- (1) Randomize intervention and control clinics:** A list of clinics that are interested in participating will be compiled by the primary investigators. A member of the study team, [name], PhD, will use the random number generator built into SAS to randomize 10 clinics into treatment and 10 clinics into control groups. If the number of potentially eligible clinics exceeds 20, 20 clinics will be chosen at random, and this list will subsequently be divided into 10 random treatment clinics and 10 random controls. Results of randomization will be provided to the study coordinators, who will inform clinics of their status.

Data for all patients who meet inclusion criteria will be included in this analysis. This educational

intervention is intended to better inform providers in intervention clinics as to the fall-related risks associated with opioids and BZDs as well as best practices in deprescribing opioids and BZDs. A toolkit to support screening and deprescribing will also be provided to providers at intervention clinics. It is expected that providers will use this information to attempt deprescribing for any patients for whom they feel the benefits of deprescribing outweigh the risks. The study team will collect data from the EHR on all potentially eligible patients, regardless of any attempted deprescribing. The same data will be collected for patients who received care from treatment and control clinics.

**(2) Screen for risk of falling:** Intervention group clinics will be expected to screen all patients who appear on the baseline report for falls risk, questions if the patient has not already been screened previously, by using the STEADI screening questions. Each clinic will be allowed to determine how they will integrate these questions into the patient care process. Although the processes used to integrate the screening questions into patient care will vary across clinics, all clinics will be required to enter patient responses to the questions into the EHR, as is standard practice in all UNC HealthCare clinics.

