**(3) Educate about opioid and BZD medications as they relate to falls:** Intervention Group clinics will be encouraged to educate all patients who appear on the baseline report for opioid and BZD use that may place them at increased risk for falls. The baseline report will include all patients in that clinic who are 65 years and older and on an opioid and/or BZD for > 6 weeks. Printed and online educational materials highlighting the risks associated with opioid and BZD use will be provided to clinics for their patients. Providers will be encouraged to use these materials in conjunction with verbal education.

**(4) Educate on overall fall prevention strategies:** Printed and online patient education materials regarding falls risk and falls prevention will be given to the intervention clinics to give to patients whom they believe would benefit from the materials. General patient education materials, not specific to opioids or benzodiazepines, will be given to all control clinics.

**(5) Implement the Deprescribing Educational Intervention:** A medication review is part of usual care conducted during a typical clinic visit. If utilized, the toolkit and associated resources can augment this process. During the medication review, the HCP (e.g. nurse, physician, pharmacist, etc.) will follow a consistent approach to patient care, reviewing the patient's medications and identifying medication therapy problems. Special attention will be given to the opioid and BZD medications that the patient is taking since these medications are the focus of this project. To improve the process of the deprescribing for opioids and BZDs, a guidance algorithm and deprescribing toolkit will be available for use. The deprescribing toolkit is being developed by the research team and is based upon evidence-based literature and clinical guidelines. For this study, we will use the toolkit to offer suggestions of medications that may assist with pain and sleep as alternatives to opioids and BZDs. We will also provide patient education materials for the clinics to give their patients. We will make revisions to the toolkit based on feedback from our provider focus group and will amend or supplement our patient education resources based on feedback from our patient focus group.

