#### **4.4 Screen failure procedures**

Providers in the intervention clinics will continue to provide usual care to all patients that do not screen into the study.

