### 6.3 Statistical Methods

**Primary Analyses:** We will examine between-group differences in opioid and BZD exposure associated with an increased risk of falls in the intervention and control groups. Analyses will be performed using the following intention-to-treat principle, and index dates for the intervention group will correspond to the date on which they first received any intervention-related clinical activity. Index dates for otherwise eligible patients from the control group will be chosen at random from each patients' set of clinic visits corresponding to an eligible intervention visit during the study period. Our primary hypotheses are:

- Relative to individuals in both control groups, individuals in both intervention groups will experience a significant reduction in the milligram equivalent exposure to opioids and BZDs during the 1-year follow-up period.

- Relative to individuals in both control groups, individuals in both intervention groups will experience a significantly greater discontinuation rate of opioids and BZDs during the follow-up period 181 to 360 days after index.

There are two overlapping groups of patients aged 65+ that will be included in this study: opioid users and BZD users. For each hypothesis, there will be separate models comparing the impact of the program on opioid users and BZD users. Patients who use both will appear in both models. To examine any differential impact of the program among patients who use both classes of medications, a sensitivity analysis will be performed and will include an indicator variable for patients who use both classes.

Generalized estimating equations (GEE, PROC GENMOD) will be used to create longitudinal pre-post model for the milligram equivalent exposure models. An identity link with a normal distribution will be used for milligram equivalent exposure. The functional form of the model is as follows:

$$\text{Eq. 1: } Y = \beta_0 + \beta_1 X_{\text{exp}} + \beta_2 X_{\text{period}} + \beta_3 X_{\text{exp} \times \text{period}} + \beta_n X_n + \epsilon$$

Where  $X_{\text{exp}}$  is the exposure group indicator,  $X_{\text{period}}$  is the pre-post indicator, and  $X_{\text{exp} \times \text{period}}$  is the period-by-treatment interaction indicator and, correspondingly,  $\beta_3$  is the parameter of the difference in outcome by period for the intervention group compared to the control.  $X_n$  represents a vector of covariates.

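### The analysis cohort is not closed before randomisation: eligibility is undated and patients get an index date only through post-allocation events that differ by arm

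*Protocol*

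**What the plan says.** All references are to the Protocol.

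- **Analysis set, section 4.2(1).** "Data for all patients who meet inclusion criteria will be included in this analysis". The same section adds: "The study team will collect data from the EHR on all potentially eligible patients, regardless of any attempted deprescribing". The same data are to be collected in both arms.
- **Eligibility, section 3.3.** Age 65 or over and "taking at least one opioid or benzodiazepine medication listed in the design section for > 6 weeks". Neither this criterion nor the problem-list exclusions carry a date of assessment.
- **Allocation.** Clinics are randomised in Year 2 (section 3.2), and the allocation is open: "Results of randomization will be provided to the study coordinators, who will inform clinics of their status".
- **Index dates, section 6.3.** In one arm, "index dates for the intervention group will correspond to the date on which they first received any intervention-related clinical activity". In the other, for patients who are otherwise eligible, the date is "chosen at random from each patients' set of clinic visits corresponding to an eligible intervention visit during the study period".
- **Baseline report, section 4.2(3).** "The baseline report will include all patients in that clinic who are 65 years and older", provided they have more than six weeks of use. Sections 4.2(2), (3) and (6) describe it as a tool with which intervention clinics screen and educate.

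**The concern.** In a cluster trial, randomisation protects the comparison for patients who could have been identified before clinics were allocated. If patients can join afterwards, through events that the allocation may influence, membership of the cohort becomes partly an outcome of the trial.

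That can happen here by two routes. First, a control patient who passes six weeks of use after launch needs only a suitable visit to receive an index date, whereas a comparable intervention patient must be reached by programme activity, which is directed mainly at patients on the baseline report. Secondly, trained prescribers who know their arm may affect who becomes a long-term user at all.

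A patient who has just become a long-term user has little exposure in the 12 months before index and possibly much more in the 12 months after it, so dose tends to rise for reasons unrelated to the programme. Such a patient may also stop more readily than an established user. If the share of these patients differs between arms, the period-by-group interaction in Eq. 1 and the discontinuation contrast at days 181 to 360 both move without any programme effect.

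**Working it through.** **Is the cohort closed anywhere?** Four places could close it:

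| Place | Dated before allocation? | Described for control clinics? | Named as the analysis set? |
|---|---|---|---|
| 3.1.3, list of potentially eligible patients | No | No, shared with intervention clinics | No |
| 4.2(2), (3), (6), baseline report | No | No | No |
| 6.6, population described as prevalent users | No | Not applicable | No, a description without a rule |
| 8, EHR data gathered at baseline and after one year | Baseline is not dated against randomisation | Yes, the trial data as a whole | No, it concerns extraction, not membership |

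None closes it. Every outcome window in section 5 is counted from index, so under section 6.3 a patient without the qualifying event cannot be analysed. Membership therefore depends on events after allocation.

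**How large could the effect be?** No figure in the Protocol depends on this point, so there is nothing to reproduce. The following is an illustration with no true effect. All its inputs are assumptions that the documents do not supply.

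Dose, counted as days of use at a constant daily dose common to both kinds of patient:

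- Established users fall 10% in both arms: −0.10 × 365 = −36.5 days.
- Late entrants, central case, have 90 days of use before index and 60% of a full year after it: 0.60 × 365 − 90 = +129 days.
- Gap between the two: 129 − (−36.5) = 165.5 days.
- False interaction = (late-entrant share in intervention − share in control) × gap ÷ 365.

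Take 20% late entrants among controls. If the intervention arm has half as many per established user, its ratio is 0.5 × 0.20/0.80 = 0.125 and its share is 0.125/1.125 = 11.1%.

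- 20% against 11.1%: −0.0889 × 165.5 ÷ 365 = **−4.0%** of annual dose.
- 20% against 0%: −0.20 × 165.5 ÷ 365 = **−9.1%**. This is the extreme for the intervention share.

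Varying the inputs:

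- The smallest gap is 0.50 × 365 − 120 + 36.5 = 99 days. With 10% in controls and half as many in the intervention arm (5.3%), the result is −0.0474 × 99 ÷ 365 = −1.3%.
- The largest gap is 0.70 × 365 − 60 + 36.5 = 232 days. With 25% against 0%, the result is −0.25 × 232 ÷ 365 = −15.9%.

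Discontinuation: shift = difference in share × (rate in late entrants − rate in established users).

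- Rates of 5% and 30%, at 20% against 11.1%: controls 0.05 + 0.25 × 0.20 = 10.0%; intervention 0.05 + 0.25 × 0.111 = 7.8%. The shift is −2.2 points, a false odds ratio of (0.0778/0.9222)/(0.10/0.90) = 0.76.
- Rates of 15% and 40% have the same 25-point gap, so the shift is again −2.2 points.
- Over the share differences above (0.0474 to 0.25), the shift runs from −1.2 to −6.25 points.

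With more late entrants among controls, dose is biased towards the programme and discontinuation against it. If the imbalance ran the other way, both signs would reverse. With equal shares, both biases are zero.

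**The case against.** The strongest reply is that the Protocol, read as a whole, intends a baseline list of prevalent users. Section 3.1.3 speaks of a list, section 4.2 of a baseline report, section 6.6 of prevalent users and section 8 of a baseline extraction. On that view only the snapshot date is missing, and a statistical analysis plan could supply it. The intent is plausible. But the Protocol does not leave the matter open: it states an analysis set and two index rules which, followed as written, admit patients after allocation. A pre-randomisation list also has to be fixed at the right time.

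Three parts of the objection stand.

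- A reader might infer that section 6.3 makes control eligibility depend on visits during the study. It does not. It ties the control **index date** to such visits, for patients otherwise eligible, and the visit must correspond to an eligible intervention visit. The visit matters because no outcome can be computed without an index date.
- A reader might treat late entry as wholly separate from the index rule. Much of any imbalance would arise through that rule. With a common rule, late entrants could still join, but unequal entry would then come mainly from a programme effect on new long-term use, for which the documents give no evidence.
- A reader might take section 4.4 ("usual care to all patients that do not screen into the study") as confirming entry through clinic activity. That sentence concerns care, not the analysis set, and need not change.

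**Conclusion.** The concern holds as a defect in how the cohort is fixed: eligibility is undated, index dates come from different post-allocation events in the two arms, and no passage names a pre-allocation list covering both. Bias in both primary outcomes is possible.

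It would go too far to say that bias is shown, or that it favours the programme. The documents give neither the share of late entrants nor how they differ from established users. The 4% and 9% figures rest wholly on the assumptions above, and 9% needs an intervention arm with no late entrants at all. For scale only, the mean reductions cited in sections 6.4.1 and 6.4.3 start at 31% for opioids and 25% for benzodiazepines. The power statements themselves are in milligram-equivalent differences of 0.30 and 0.25, so the percentages are not directly comparable with them. The change is worth making because it is cheap and removes the problem whatever its size.

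**What to change.** In section 4.2(1), replace the sentence defining the analysis set with wording such as: *The primary analysis cohort is all patients who meet the inclusion and exclusion criteria in one EHR query, run identically in all 20 clinics at a single cut-off date before randomisation. Each patient is analysed in the clinic and arm attributed on that date, regardless of later visits, screening or treatment.* If the query must be run nearer launch, judge eligibility only on prescriptions dated before allocation. State whether the baseline report is this query.

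In section 6.3, state that both arms come from this list, and define the index date in the same way in both arms so that every listed patient has one. The common programme launch date would do. This second step is essential: without it, listed patients who are never visited or reached have no 12-month or day 181 to 360 window. Patients who first qualify later can be described separately.

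With the cohort closed, the late-entrant share is zero in both arms and the bias terms above vanish.

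The cost is Protocol wording and the same query in the control clinics. The cohort may be somewhat smaller. The estimated effect will be diluted by listed patients whom the programme never reaches. Because randomisation falls in Year 2 and launch in its seventh month, the list may be some months old at launch.

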### **Exclusion Criteria**

Clinics that do not provide primary care services will be excluded from participating in the study.

Patients who exhibit signs of cognitive impairment or speech/hearing deficits that make obtaining informed consent and completing data collection activities difficult; patients undergoing active cancer treatment, receiving hospice care, or living in a skilled nursing facility; and non-English speaking patients will be excluded from participating in the patient focus group. Participants who do not wish to be audio-recorded during focus group sessions will also be excluded.

Patients who exhibit signs of cognitive impairment; are non-English speaking; or are undergoing active cancer treatment, receiving hospice care, or living in a skilled nursing facility will be excluded from the deprescribing intervention.

---

|                                                               |                                                                                                                                                                                                                                                                                                                                                                                                                                                   |
|---------------------------------------------------------------|---------------------------------------------------------------------------------------------------------------------------------------------------------------------------------------------------------------------------------------------------------------------------------------------------------------------------------------------------------------------------------------------------------------------------------------------------|
| Number Of Subjects                                     | Focus groups: 12 healthcare professionals and 12 patients.
Web-based survey: 120 healthcare professionals
Cluster-randomized trial: Total number of clinics (intervention & control): 20; Total number of patients (intervention and control): 3,000                                                                                                                                                                   |

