### 3.1.3 Cluster-Randomized Trial:

This **cluster-randomized trial** will use a longitudinal pre-post research design. Data will be collected from two groups (1 intervention and 1 control) with three comparisons. The groups will be comprised of primary care outpatient clinics within the UNC HealthCare System, including family medicine, primary care, and geriatric clinics. Clinics will be randomly selected into either intervention or control clinics. Study team members will work with providers at intervention clinics to implement the educational intervention, which is designed to reduce falls risk through opioid and BZD deprescribing. Potentially eligible patients will be shared with physicians at intervention clinics. Emphasis will be placed on this list as a potential list; in no way are the study team mandating providers to de-prescribe opioids or BZDs in these patients. The decision to de-prescribe is left solely to the provider.

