#### **Exclusion Criteria:**

Clinics that do not provide primary care services will be excluded from participating in the study.

Patients will be excluded from the focus groups if they are not English speaking, exhibit signs of cognitive impairment or speech/hearing deficits, are undergoing active cancer treatment, receiving hospice care, live in a skilled nursing facility, or do not wish to be audio-recorded.

Patients will be excluded from the cluster-randomized trial analysis if their EHR problem list indicates they have cancer, cognitive impairment, are receiving hospice care, live in a skilled nursing facility, or are non-English speaking.

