HCPs performing the opioid and BZD medication reviews will be trained by research personnel (see *Training of Personnel*) to use the toolkit to guide the assessment of opioid and BZD use, the assessment of the patient's risk of falls, and the development of recommendations including possible non-pharmacological interventions they can introduce. In all cases, however, the HCPs will be trained to use their clinical judgment and weigh the risk versus benefit of a medication change before making a recommendation. If the need for a reduction in opioid or BZD dose is warranted, the reasoning and potential solutions will be discussed with the patient. As part of this discussion, the HCP will assess patient willingness to make recommended changes to their medication regimen. As appropriate, patient preferences will be incorporated into recommendations implemented. Patients will receive follow-up from the clinic within a timeframe that fits with the deprescribing strategy employed and which the provider and patient agree upon. During the assessment phase, the provider will also solicit information from the patient concerning medical problems associated with an increased risk of falls (e.g., orthostatic hypotension, nocturia) and provide fall prevention education based on the STEADI resources provided in the toolkit.

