**(6) Training of Personnel.** All personnel at Intervention Group clinics will be required to take part in an educational training session, which will include information about the study's purpose, general processes, and available resources. The training session will include physicians, physician assistants, nurse practitioners, nurses, pharmacists, technicians, medical assistants, office managers, case managers and quality improvement officers. Following the training, clinic staff will be able to (1) administer the three STEADI screening questions to all older adults identified in the baseline reports generated by Epic EHR data; (2) identify patients who qualify for the deprescribing intervention; (3) provide patients education about the risks associated with opioid use, BZD use, and falls; and (4) utilize the toolkit and associated resources to effectively and safely deprescribe opioids and BZDs when warranted. Special emphasis will be placed on sharing non-pharmacological recommendations with patients as alternatives to medications associated with an increased risk of falling. Finally, we also will provide in the toolkit - for clinicians interested in learning more - primary literature and other resources related to deprescribing.

**(7)** Following launch of the study, continuous quality improvement processes will be initiated. Specifically, a postdoctoral fellow based in the central project office will contact each intervention clinic within one week of the implementation of the intervention, then monthly thereafter. The phone contact will enable clinic personnel to: (1) ask and have answered any questions they may have about study procedures and (2) report unforeseen issues that need to be addressed, including safety concerns related to deprescribing. The fellow will also conduct clinic site visits if needed to resolve unforeseen problems and maintain engagement and fidelity for the duration of the project.

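### The report sent to intervention clinics carries none of the protocol's exclusions, and cancer is defined differently for the intervention and for the analysis; one EHR filter and one cancer definition would mend most of this (minor)

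*Protocol*

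**What the plan says.** Three parts of the protocol decide which patients are reached or counted.

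- **The list.** Section 4.2 (3): "The baseline report will include all patients in that clinic who are 65 years and older and on an opioid and/or BZD", with more than six weeks of use as the only further condition. Section 4.2 (2) expects intervention clinics to screen everyone on this report who has not already been screened, and section 4.2 (3) encourages clinics to educate everyone on it.
- **The intervention.** The synopsis exclusion criteria cover "Patients who exhibit signs of cognitive impairment; are non-English speaking" and add that those "undergoing active cancer treatment, receiving hospice care, or living in a skilled nursing facility will be excluded from the deprescribing intervention".
- **The analysis.** Section 3.3: "Patients will be excluded from the cluster-randomized trial analysis if their EHR problem list indicates they have cancer, cognitive impairment", followed by hospice care, skilled-nursing residence and not speaking English.

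Between the list and any taper, the protocol relies on the clinic. Section 3.1.3 says "Emphasis will be placed on this list as a potential list". Section 4.2 (5) says "the HCPs will be trained to use their clinical judgment and weigh the risk versus benefit of a medication change before making a recommendation". Section 4.2 (6) trains staff to "identify patients who qualify for the deprescribing intervention". Section 4.4 leaves patients who do not screen in to usual care.

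**The concern.** The protocol protects certain patients from the deprescribing intervention, yet its rule for the report puts them on the list from which that intervention starts. Most of these conditions are ones that section 3.3 already expects to read from the EHR, and section 4.2 (6) says the report itself is generated from Epic data, so they could be removed before the list leaves the study team.

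Separately, the intervention and the analysis use different meanings of cancer. Some patients who may properly be deprescribed contribute nothing to the dose, discontinuation or falls results. Those results then describe a somewhat different population from the one treated.

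**Working it through.** The protocol gives no figure on this point, so the check is a comparison of the rules.

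| Condition | List, section 4.2 (3) | Intervention, synopsis | Analysis, section 3.3 |
|---|---|---|---|
| Hospice care | not excluded | excluded | excluded |
| Skilled nursing facility | not excluded | excluded | excluded |
| Non-English speaking | not excluded | excluded | excluded |
| Cancer | not excluded | excluded if on active treatment | excluded if the problem list indicates cancer |
| Cognitive impairment | not excluded | excluded on signs | excluded on a problem-list entry |

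Following typical patients through the rules:

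1. *Hospice patient aged 65 or over on an opioid for more than six weeks.* Listed, due for screening and education, barred from deprescribing, not analysed. A non-English speaker follows the same path. So does a skilled-nursing resident, with one reservation: section 3.3 describes targeted patients as ambulatory and not institutionalised, but the list rule does not carry that condition.
2. *Patient with current cancer on the problem list and no active treatment.* Listed, may be deprescribed, not analysed. Whether a past cancer entry also counts is not settled by the text.
3. *Patient with signs of cognitive impairment and no entry.* Listed, barred, analysed.

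What stands between the list and a taper for patient 1:

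- The bar appears only in the synopsis. Section 3.3 gives exclusions for clinics, focus groups and the analysis, but none for the intervention.
- Section 4.2 (6) trains staff to find who qualifies without stating the criteria. Section 4.2 (1) frames the decision as the provider's weighing of benefit against risk.
- Patients are not recruited (section 9) and do not consent (section 10), so no enrolment step checks eligibility.

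Removal of barred patients therefore rests on clinic judgement alone.

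**Size.** The protocol gives no prevalence for any of these groups, and section 3.2 does not say whether its 3,000 patients are counted before or after exclusions. For scale only, suppose 3,000 is before exclusions and is split equally, as section 6.4 assumes. Then 3,000 / 2 = 1,500 patients are in the intervention arm. Each 1% of listed patients with cancer but no active treatment is 0.01 × 1,500 = 15 patients, or 15 / 10 = 1.5 per intervention clinic. The true percentage is unknown.

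**The case against.** The best reply is that this is an ordinary two-stage screen. The list is called potential, staff decide who qualifies, risk and benefit are weighed in every case, and those who do not qualify get usual care. A candidate list may be wider than the eligible set. The report also drives falls screening and education, from which the synopsis does not bar anyone, and a hospice or non-English-speaking patient may benefit from a falls prompt. A bedside rule and a coded rule serve different purposes, so some difference in wording is natural.

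Much of this stands. The list mandates no taper, and filtering it has a real cost in lost prompts. It does not remove the point, because none of the clinic-level steps restates who is barred and the two cancer definitions remain apart.

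Three stronger readings are tempting and are not supported:

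- *That barred patients will be deprescribed.* Sections 3.1.3, 4.2 (5), 4.2 (6) and 4.4 provide a clinic-level step, and no harm from screening or leaflets is shown.
- *That the comparison is biased.* The analysis exclusions in section 3.3 are worded alike for both arms.
- *That section 4.2 (1) contradicts section 3.3* because it says "Data for all patients who meet inclusion criteria will be included in this analysis" and mentions no exclusions. Read together, the two sections are compatible.

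The protocol also does not say at which date the analysis exclusions are read. That detail is commonly left to the SAP, so it is not held against the protocol, though the fix has to settle it.

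**Conclusion.** The concern holds as a minor point of safety and consistency. By its stated rule, the report includes patients whom the synopsis bars from deprescribing; only clinic judgement takes them off, and the bar is missing from section 3.3 and the training text. Patients with cancer but no active treatment may be deprescribed yet are not analysed.

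This rests on reading the list rule in section 4.2 (3) as written and not as shorthand for the target population in section 3.3. Even the shorthand reading would cover only institutionalised patients and would leave the cancer mismatch untouched. The number of patients involved is unknown, so no effect on power or on the estimates can be claimed.

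**What to change.** 1. In the Epic query that builds the baseline report, exclude patients with hospice care, skilled-nursing residence, cancer, recorded cognitive impairment or non-English language. Run the same query in the control clinics without sending the list.
2. Use one cancer definition for the list and the analysis. Problem-list cancer is the simpler choice because section 3.3 already uses it. If the sponsor prefers active treatment, use that in both places, provided the EHR can support it.
3. Read exclusion status in both arms no later than the index date, never from the EHR draw that section 8 plans after the intervention year. The later draw would drop patients who entered hospice or a nursing facility during follow-up, against the intention-to-treat principle in section 6.3.
4. Repeat the synopsis bar in section 3.3 and in the training text as a clinic-level safeguard. Patients barred later stay in the intention-to-treat analysis.

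The cost is protocol wording, a filter in an existing query and one run of it in the control clinics, with no added patients or visits. There are three downsides. Filtered patients lose the study's prompt for falls screening and education, although usual care continues. Inaccurate problem lists will misclassify some patients in both arms. Signs of cognitive impairment without an entry cannot be filtered and remain a clinic check, so that mismatch between the intervention and analysis rules persists.
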